## Abstract

**Background:**

Preterm infants follow an altered neurodevelopmental trajectory compared to their term born peers as a result of the influence of early birth, and the altered environment. Infant massage in the preterm infant has shown positive effects on weight gain and reduced length of hospital stay. There is however, limited current evidence of improved neurodevelopment or improved attachment, maternal mood or anxiety. The aim of this study is to investigate the effects of infant massage performed by the mother in very preterm (VPT) infants. Effects on the infant will be assessed at the electrophysiological, neuroradiological and clinical levels.  Effects on maternal mood, anxiety and mother-infant attachment will also be measured.

**Methods/Design:**

A randomised controlled trial to investigate the effect of massage therapy in VPT infants. Sixty VPT infants, born at 28 to 32 weeks and 6 days gestational age, who are stable, off supplemental oxygen therapy and have normal cranial ultrasounds will be recruited and randomised to an intervention (infant massage) group or a control (standard care) group. Ten healthy term born infants will be recruited as a reference comparison group. The intervention group will receive standardised massage therapy administered by the mother from recruitment, until term equivalent age (TEA). The control group will receive care as usual (CAU). Infants and their mothers will be assessed at baseline, TEA, 12 months and 24 months corrected age (CA), with a battery of clinical, neuroimaging and electrophysiological measures, as well as structured questionnaires, psychoanalytic observations and neurodevelopmental assessments.

**Discussion:**

Optimising preterm infant neurodevelopment is a key aim of neonatal research, which could substantially improve long-term outcomes and reduce the socio-economic impact of VPT birth. This study has the potential to give insights into the mother-baby relationship and any positive effects of infant massage on neurodevelopment. An early intervention such as massage that is relatively easy to administer and could alter the trajectory of preterm infant brain development, holds potential to improve neurodevelopmental outcomes in this vulnerable population.

**Trial registration:**

Australian New Zealand Clinical Trials Registry: ACTRN12612000335897. Date registered: 22/3/2012.

## Background

Over the past 50 years, there has been a progressive decrease in preterm infant mortality [1]. A lowering of the age limit of viability and an increase in preterm birth numbers has made preterm birth a significant public health issue [1]. Despite advances in technology, the number of preterm infants with neurodevelopmental compromise remains high [2]. In recent years the focus of improving preterm outcomes has shifted from increasing survival to minimising morbidity and improving neurodevelopmental outcomes [1, 3]. Long term neurodevelopmental abnormalities impact up to 50 % of these infants [4] and include motor disability (including cerebral palsy), reduced cognitive performance and behavioural problems [3]. The severity of the deficits is related to the degree of prematurity and the presence of neuroradiological injuries [3], however high rates of more subtle but nonetheless important neurodevelopmental abnormalities also occur in low-risk preterms without obvious brain injury [5, 6]. Even in late preterm infants, the effects of preterm birth on brain development are more significant and long lasting than previously thought [5, 7]. The untimely interruption of the developing fetus’ environment is thought to be a major contributor to this phenomenon [6].

### Disruption of optimal fetal environment

The altered neurodevelopmental trajectory observed in preterm infants results from interruption of the intrauterine environment. The neuromaturation of the cerebral cortex, initially laid down in cortical layers prior to 20 weeks gestation, is a dynamic process from 30 to 40 weeks gestation. It is during this time, the subplate, a transient population of neurons, guides the development of cortical and thalamocortical connections [8], maturing from its maximal prominence to almost complete regression. These connections are fundamental for cortical processing and cognition [8]. Between 29 and 41 weeks, total brain volume is increased nearly 3-fold, cortical gray matter volume is increased 4-fold and cerebellar volume is increased 4-fold [7]. Although some differences between term infants and preterm infants at term equivalent age are explained by the effect of complications associated with preterm birth, both the experience of a highly stressful ex-utero environment and the lack of the stimulation normally experienced in the womb, exert detrimental effects on the immature brain [6, 9]. The challenges imposed by the extra-uterine environment, disrupt the above described development of a “neurotypical” brain. Results include numerous primary medical problems experienced by preterm infants such as lung disease of prematurity, physiological instability, asphyxia, suboptimal nutrition, infection, medication side effects and hyperbilirubinaemia, each of which may have its own potentially deleterious impact on brain development [6, 10]. Environmental stressors, which include frequent noxious stimulation, excessive sound and constant light, also adversely affect the normal neurodevelopmental trajectory [6, 10]. Repetitive pain universally experienced by premature infants from frequent invasive procedures is hypothesised to cause excessive activation of central afferent pain pathways and excitotoxic damage to the developing brain [11]. While the impact of these factors and negative influence on the brain are recognised, emergent strategies to lessen harm include environmental enrichment and infant massage.

### Environmental enrichment

Environmental enrichment and social stimulation induce experience-dependent neuroplasticity in experimental animal models [10]. Neuroplasticity is the capacity of the mammalian brain to use the activity induced by a given experience, enabling the modification of function in neuronal circuitry [12]. Early interventions based on the manipulation of the extra-uterine environment, among them infant massage therapy, have been used in preterm infants with the aim of optimising the infant’s sensory experience and improving overall functional outcome [13, 14].

### Infant massage

Infant massage has been investigated as a potentially effective intervention aimed at providing a form of environmental enrichment [15]. It is often combined with other forms of stimulation such as kinaesthetic stimulation (e.g. passive extension/flexion movements of the arms and legs), talking or eye contact [16]. The possibility that infant massage could provide a form of comforting touch with positive effects on growth and neurodevelopment is described in a number of studies [16, 17]. Evidence supporting positive effects of massage in preterm infants include increased weight gain [18–20], improved growth and gastrointestinal function [21, 22], improved body fat deposition [23], improved neurobehavioural outcomes [17, 24–26], pain attenuation [27, 28], reduction of infant stress and stress-related factors [29, 30], reduction of late-onset sepsis [31], improved immune system [32], reduced jaundice [33] and improved heart rate variability [34] as well as a reduction in maternal depression and anxiety [35]. Studies investigating the use of specific oils in massage versus no oil suggest improved weight gain [36–38]. Overall the evidence remains weak, mainly due to small sample sizes, heterogeneity and poor methodology in some studies. The current level of evidence does not support wider use of infant massage without further research [17, 39]. Two key aspects of infant massage as an early intervention have received little attention. The first aspect is the effect of infant massage on direct measures of brain development, such as the maturation of brain electrical activity, brain structure and the relationship to clinical neurobehaviour. A recent meta-analysis reported that the association between massage and neurobehavioural development remained elusive [40]. The second aspect is the potential to enhance the efficacy of the intervention by active involvement of the parents; in particular the mother, and what effect of actively massaging her baby may have on the mother-infant relationship.

### Clinical neurodevelopmental assessments

Traditionally, methods of neurodevelopmental assessment of the preterm infant have included a number of clinical examinations used to evaluate neurological function and neurobehaviour [41]. Those most commonly used in the neonatal period include the Prechtl’s General Movements Assessment (GMA), Hammersmith Neonatal Neurological Examination (HNNE), Amiel-Tison Neurological Assessment at term, Neonatal Behavioural Assessment Scale (NBAS), Neurobehavioural Assessment of the Preterm Infant (NAPI) and the Neonatal intensive care unit Network Neurobehavioural Scale (NNNS) [42]. These assessments vary in the time required for training, as well as in the appropriate age of administration and scoring systems. This affects the ability to use them in clinical practice or research [42]. The Prechtl’s GMA has the greatest predictive accuracy for the diagnosis of cerebral palsy [41, 43] with a sensitivity of 98 % and specificity of 91 % [44]. The assessment is based on a global visual perception system of the quality and complexity of movements [45]. As such, it is an applicable tool to use evaluating the impact of massage.

Much like the rest of the brain, considerable development of the visual system occurs in the third trimester, which increases the potential for long-term visual dysfunction in preterm infants. The Neonatal Vision Scale is an assessment that was originally developed to test vision in full term infants. It has subsequently been applied to preterm infant cohorts to reliably measure the integrity of the visual system [46, 47]. Using this scale could assist in evaluating any measureable effects of massage on the visual system.

Measuring long-term neurodevelopmental outcomes has been standardised for a number of assessments for use in toddlers and young children. These assessments are particularly useful for assessing high-risk populations such as VPT infants. The Bayley Scales of Infant and Toddler Development, Third Edition (Bayley-III) is a structured instrument to assess cognitive and social-emotional development, language and motor abilities [48] and is the most widely used measure to assess neurodevelopment of VPT and very low birth weight infants in the first three years [49]. In a recent review, Mental Development Index (MDI) scores were strongly predictive of later cognitive functioning, r = 0.61 (95 % CI = 0.57-0.64) and motor scale scores were moderately predictive of later motor function, r = 0.34 (95 % CI = 0.26-0.42) [49]. In another recent study [25], 73 very low birthweight preterm infants who had been randomised to receive massage therapy or not, were followed up at 2 years of age with the Bayley Scales of Infant Development Second edition (BSID-II). Outcomes showed the Mental Development Index (MDI) was higher in the intervention group than the control group indicating better cognitive scores in the group who received massage [25]. In the present study, we will use Bayley-III to review these findings.

### Magnetic Resonance Imaging to assess structure

Magnetic Resonance Imaging (MRI) has become an essential neurodiagnostic tool as it offers high resolution images and can assist prognostication following neonatal brain injury [50]. MRI studies in preterm infants at term-equivalent age have shown that preterm birth alters development of regional brain volume [51], white matter [52–54], cortex [55, 56], deep gray matter [57, 58] and vascular organisation [59]. With diffusion tensor imaging, white matter integrity and white matter maturation can be studied, and white matter pathways can be non-invasively delineated through diffusion tractography [60–62]. Numerous studies have evaluated the ability of MRI at term equivalent age to predict neurodevelopmental outcomes at 1 to 9 years and established it as the best imaging tool available for outcome prediction of children born preterm [63]. To our knowledge, MRI studies of infants who have received massage therapy are yet to be described.

### Electroencephalography to assess function

Electrophysiological studies have reported significant differences in spectral electroencephalography (EEG) measures between healthy term and preterm infants [64–66]. Maturation of the EEG in preterm infants is characterised by decreases in the total amplitude and delta activity power in quiet and active sleep [67]. A preliminary study examining whether preterm infant massage has a beneficial effect on cerebral function as measured by EEG, found a significant difference in the interburst interval duration and also a difference in maturation of visual function in preterm infants who received massage in comparison to preterm infants who received standard care [68]. A subsequent study showed a relative increase in global EEG spectral power in delta and beta frequencies in massaged infants when compared to controls, which was interpreted as suggesting that massage therapy in low-risk preterm infants favors a process of maturation of brain electrical activity similar to that observed in term born infants [24].

### Parental stress, infant attachment and related assessments

The stress and trauma of VPT birth on the parents is well described [69–72]. Preterm delivery has been identified as a risk factor for stress, postpartum posttraumatic stress disorder, postpartum depression and difficulty with initial bonding and attachment [73]. The increased levels of stress, anxiety and depression may negatively influence the already difficult maternal-infant bonding [73]. Historically, a high dependence on technology for life-support, the institutionalisation of preterm infant care and the fear of infection have often resulted in the separation of mother and baby [74]. In the early 1970s, research demonstrated that mothers who were permitted to enter the nursery showed a greater commitment to their infants, were more confident in their mothering abilities and had increased caretaking skills [74]. In response to this and subsequent evidence, parental involvement was encouraged [74].

An increase in bonding and attachment behaviours and a decrease in parental depression has been reported in studies where mothers attended massage classes 2 months after birth at term [75]. In the same way, actively providing infant massage could help to mitigate the impact of stress and anxiety in the intensive care nursery environment, by allowing mothers to be more proactive in the developmental care of their babies. A variety of maternal factors including frequency of maternal touch and the degree of postpartum depression (PPD) can influence the neurodevelopmental and cognitive skills of the preterm infant [76, 77].

Maternal mood and anxiety have been measured using a number of scales. The most widely researched is the Edinburgh Postnatal Depression Scale [78] which demonstrates moderate to good internal consistency over several studies. Other measures such as the Postpartum Depression Screening Scale (PDSS) and the Beck Depression Inventory (BDI) are also widely used and demonstrate good concurrent validity [78].

The Depression Anxiety Stress Scale (DASS) is another widely studied assessment tool in the postnatal period. It is a 42-item questionnaire, completed by the mother, designed to measure the magnitude of these three negative emotional states [79, 80]. The Depression scale focuses on reports of low mood, motivation and self-esteem, the Anxiety scale assesses physiological arousal, perceived panic and fear, and the Stress scale measures tension and irritability [79, 80]. Internal consistency for each of the subscales is typically high (e.g. Cronbach’s α of 0.96-0.97, 0.84-0.92, 0.90-0.95 for Depression, Anxiety and Stress respectively) [80] and convergent and discriminant validity has been demonstrated [81].

Attachment difficulties can arise from preterm birth disrupting normal physical contact between the mother and infant [82] and withdrawal of the mother from their infant due to distress [83]. This may inhibit the mother’s caregiving behaviour as her desire and ability to provide protection for her preterm infant is interrupted, ultimately impacting the mother’s attachment representations and the child’s attachment patterns [84]. Infant Observation is a method developed by Esther Bick at the Tavistock Clinic in London more than 60 years ago, and has been used to understand the characteristics of the developing relationship between mother and infant [85]. This method has been widely used internationally for training and research in the psychodynamic-psychoanalytic field to capture the rich and complex nature of mother-infant attachment. One of these complexities in particular is that of maternal responsiveness.

Maternal responsiveness plays an important role in developing secure attachment and effective bonding patterns between mother and infant. Ineffective maternal responsiveness is directly related to a lack of attachment, low self-esteem and unhealthy growth and development of the child [82]. The Maternal Infant Responsiveness Instrument (MIRI) was designed to measure this concept by appraising the maternal awareness and reflection of the mother’s responsiveness to her infant and her recognition of her infant’s responsiveness to her. It is easy to administer and has an alpha reliability coefficient of 0.86 [82]. The Maternal Postnatal Attachment Scale (MPAS) is designed to evaluate maternal emotions and cognitions relating to attachment. It is specifically designed for use during the first year of life and focuses on the mother’s subjective experience in relation to her infant. Internal consistency as measured by Cronbach’s coefficient alpha is 0.78. In addition to maternal attachment, this research is also aimed to explore infant mental health.

Evaluating the infant’s social and emotional functioning can be an indirect measure of the integrity of infant attachment. It has been observed that secure infant attachment status is related to lower risk for later peer interaction and behavioral problems [86]. The Infant Toddler Social and Emotional Assessment (ITSEA) is a robust parent-report questionnaire designed to assess a wide array of social-emotional and behavioural problems and competencies [87]. Its psychometric properties are sound with strong test-retest reliability (0.61-0.91, mean = 0.79), with concurrent and discriminant validities (α = 0.69-0.86, mean = 0.76) [87].

In this project we will investigate several key aspects of the effect of infant massage on preterm neurodevelopment, its neurobiological correlates and the mother-infant relationship.

### Aim

The broad aim is to investigate the potential effects of infant massage performed by the mother, in VPT infants born between 28 and 32 weeks and 6 days gestational age. Effects on the infant will be assessed at the electrophysiological, neuroradiological and clinical levels at term equivalent age and 24 months corrected age. In addition, the impact of infant massage implemented by the mother on maternal mood and anxiety and infant attachment will be measured at term equivalent age, 12 months corrected and 24 months corrected age.

### Hypothesis

The primary hypothesis to be tested is that infant massage by the mother in VPT infants promotes favourable processes in brain development, which can be functionally measured with dense array electroencephalography (dEEG).

Secondary hypotheses to be tested include the following:Infant massage by the mother in VPT infants promotes favourable processes in brain development, which can be detected structurally at term equivalent age, and functionally at term equivalent age and 24 months corrected age.Infant massage by the mother in VPT infants reduces maternal depression, anxiety and stress associated with preterm birth.Infant massage by the mother in VPT infants enhances infant attachment.

## Methods

### Design

A randomised controlled trial will be conducted to investigate the effect of infant massage. Infants will be recruited and randomised to an intervention group (PREMM), which will receive infant massage by the mother or a control group, which will receive care as usual (CAU). A study coordinator, who is not involved in generating the randomisation sequence, will assess infants for eligibility and obtain written informed consent from the parent(s).

### Participants

#### Preterm participants

Preterm infants born between 28 weeks and 32 weeks and 6 days gestational age, admitted to the Grantley Stable Neonatal Unit at the Royal Brisbane & Women’s Hospital will be assessed for eligibility. Parents will be approached for consent if a head ultrasound around day 10 after birth confirms the absence of moderate or severe intraventricular haemorrhage (> grade II) [88], periventricular echogenicity or periventricular cysts. Once written informed consent is obtained, baseline measures will be collected before allocation occurs. Allocation will be performed by opening the next, in sequence, opaque envelope by non-study personnel. In this way infants will be randomised into a massage group or a care as usual group.

##### Inclusion criteria

Infants born between 28 and 32 weeks and 6 days gestational age, with a birthweight between the 10^th^ and 90^th^ percentile (for their gestational age and gender), who are clinically stable, off oxygen therapy or respiratory support and have no IVH greater than grade II. The cut-off age for recruitment is 34 weeks and 3 days old, to ensure ample time for infants in the massage group to receive the intervention.

##### Exclusion criteria

The presence of abnormalities on brain ultrasound including intraventricular haemorrhage (grade III and IV), periventricular echogenicity or periventricular cysts. Infants with major genetic disorders and malformations will also be excluded.

### Sample size

Preliminary data from a pilot study, which described global spectral EEG power-associated brain maturation in massaged preterm infants, was used to calculate a sample size [24]. To find a 10 % between-group difference in EEG power in the treatment group [24], with type 1 error rate 0.05, and power of 80 %, we require 20 participants in each group to complete the study. Assuming that two thirds of participants will remain in the study at term equivalent age, we will require a total of 60 preterm infants to be recruited (i.e. 30 per group).

### Randomisation

Randomisation will be performed in Statistics Package for the Social Sciences (SPSS) 15.0 (SPSS Inc., Chicago, IL, USA) using random number generation with stratification by gender. The ratio of intervention to care as usual participants will be 1:1. A third party not involved with recruitment will generate the randomisation list and the list will be concealed. After random allocation lists have been generated, the allocation group (intervention or care as usual) of the premature infants will be stored in sequentially numbered, sealed, opaque envelopes. These envelopes will be opened by non-study personnel at each study enrolment, after baseline measures have been obtained.

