### Data analysis

Summary statistics will be used to describe demographic and clinical data characteristics at baseline by allocated study treatment. Continuous data will be summarised using either mean and standard deviation, or median and inter-quartile range, depending on the distribution of the variable of interest. Categorical data will be presented as frequencies and percentages. Comparisons between the baseline values of the treatment groups will be conducted to assess the degree to which variables are comparable after randomisation. Between group differences will be investigated using linear regression for continuous data and Fisher’s exact test for categorical data. Potential confounding variables for the primary outcome are considered a-priori to be: gestational age at birth, birthweight, parity and maternal education. If any of these variables differ significantly between-groups (at *P* < 0.005), the identified variable(s) will be controlled for in the main analyses.

The primary study outcome is beta frequency global power measured in all VPT infants at term equivalent age. The mean difference between treatment groups will be calculated using linear regression with treatment group entered as the main effect. The corresponding 95 % Wald confidence interval and *p*-value will be reported. For secondary outcomes, we will present the effect estimate relating to a variable with a continuous outcome as a mean difference, which will be calculated using a linear regression model. If a continuous variable does not meet the assumptions necessary for linear regression, we will compare groups using the Mann–Whitney U Test. We will present the effect estimate relating to a variable with a binary outcome as an odds ratio, which will be calculated using a logistic regression model. We will present the effect estimate relating to a variable with a count outcome as an incident rate ratio, which will be calculated using a Poisson regression model. For all models the corresponding 95 % Wald confidence interval and p-value will be reported.

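### Gestational age, the first-named confounder, is neither balanced by the randomisation nor reliably adjusted for, because adjustment waits for a baseline difference at P < 0.005

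*Protocol article*

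**What the plan says.** The Randomisation section sets the ratio ("The ratio of intervention to care as usual participants will be 1:1") and generates the list "using random number generation with stratification by gender". Gender is the only factor named.

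The Data analysis section lists the confounders for the primary outcome as "considered a-priori to be: gestational age at birth, birthweight, parity and maternal education". Adjustment is conditional. It opens with "If any of these variables differ significantly between-groups", sets the level at P < 0.005, and ends "the identified variable(s) will be controlled for in the main analyses". If nothing passes that test, the primary model is the one described as follows: "The mean difference between treatment groups will be calculated using linear regression with treatment group entered as the main effect". Neither gestational age nor gender is named as a standing covariate.

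Eligible infants are born from 28 weeks to 32 weeks and 6 days (Inclusion criteria). The Sample size section plans 60 infants, 30 per group, with 20 per group expected to complete.

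**The concern.** The plan treats gestational age as a likely source of confounding, and its Background links prematurity to outcome: "The severity of the deficits is related to the degree of prematurity". A trial this small can drift apart by several days of mean gestation by chance alone. Two tools could deal with that: balance in the design, or a prespecified covariate in the model. The plan uses neither for gestational age except in an extreme case.

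Under sound randomisation, a test at P < 0.005 fires in about 0.5% of trials by construction. The size of the baseline P-value is also a poor guide to whether a covariate matters. That depends on how strongly the covariate predicts the outcome. Conditional adjustment therefore gives up precision that a baseline value already being collected could supply. It also leaves the result open to dispute if the arms differ visibly but not at P < 0.005.

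**Working it through.** **Inputs from the protocol article.** 20 completers per group, two-thirds retention, a 10% target difference, alpha 0.05 and 80% power (Sample size); two-tailed tests and the P < 0.005 trigger (Data analysis); 35 eligible days of gestation, 28+0 to 32+6 (Inclusion criteria).

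**Assumptions, because the article gives no figure.** Gestational age is uniform over the 35 days, loss is at random, and the correlation r between gestational age and outcome is 0.2 to 0.6.

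**The plan's own figure.** 20 / (2/3) = 30 per group, 60 in total. This agrees. The 20 per group cannot be checked directly because no SD is stated. By the normal approximation it implies an SD of 10 / [(1.96 + 0.84) × √(2/20)] ≈ 11.3%.

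**Spread of gestational age.** SD = √[(35² − 1)/12] = 10.1 days.

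**Chance imbalance.** The standard error of the difference in means is SD × √(2/n).
- 30 per arm: 10.1 × √(2/30) = 2.6 days. P(5 days or more) = P(|Z| ≥ 1.92) = 5.5%; P(7 days or more) = 0.7%.
- 20 per arm: 10.1 × √(2/20) = 3.2 days. P(5 days or more) = P(|Z| ≥ 1.57) = 11.7%; P(7 days or more) = 2.8%.

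Simulation with gender-stratified blocks of 4 and one third lost at random gives the same 20-per-arm picture: SD 3.2 days, and 5 days or more in 11 to 12% of trials.

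**Difference needed to trigger adjustment.** t(0.9975) × √(2/n) in SD units.
- 30 per arm: 2.918 × 0.258 = 0.75 SD = 7.6 days.
- 20 per arm: 2.980 × 0.316 = 0.94 SD = 9.5 days.

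In simulation the trigger fires in about 0.6% of all trials. Among trials with an imbalance of 5 days or more at term equivalent age, it fires in only about 5 to 6%.

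**Sensitivity to the uniform assumption.** The thresholds in SD units do not depend on it. If the SD were 8 days, the trigger at 30 per arm would be 0.75 × 8 = 6.0 days. The chance of 5 days or more at 20 per arm would be P(|Z| ≥ 5/2.53) = 4.8%.

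**Effect on the estimate.** An imbalance of 0.5 SD (about 5 days) shifts the unadjusted difference by r × 0.5 × 11.3. That is 1.1, 2.3 or 3.4 percentage points for r = 0.2, 0.4 or 0.6, against a target of 10%.

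**Gain from always adjusting, 20 per arm.** The standard error is multiplied by about √[(1 − r²)(1 + k/36)]. Here 36 is the residual degrees of freedom (40 − 4). The penalty k lies between 1 (gender nearly balanced by design) and 2.
- r = 0.2: 0.99 to 1.01, about unchanged.
- r = 0.4: 0.93 to 0.94, a fall of 6 to 7%.
- r = 0.6: 0.81 to 0.82, a fall of 18 to 19%.

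**Gain from stratifying as well.** Adding two gestational-age bands to the list cuts the SD of the imbalance from 3.2 to 2.4 days, and the chance of 5 days or more to about 3 to 4%. Once gestational age is a covariate, however, the standard error at r = 0.6 only moves from 0.257 to 0.256.

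**The case against.** A reader might infer that the plan contradicts itself, because its only stratification factor is missing from its confounder list, and that it therefore balances the wrong factor. The text does not support this. The list names variables to be checked for chance imbalance. A factor already balanced by design need not be on it, and one left unstratified belongs there. Stratifying by gender is legitimate, and keeping strata few with 60 infants is defensible.

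A reader might also infer that the comparison is biased. It is not: randomisation keeps the estimate unbiased on average and the test valid, and imbalances of a week or more are uncommon.

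The Background sentence should not be pressed too far. It goes on to name neuroradiological injury alongside prematurity, and this trial excludes severe haemorrhage and periventricular lesions. The article gives no relation between gestational age and beta power within the eligible range. The EEG is recorded at 39 to 42 weeks postmenstrual age in every infant, which limits differences in maturity. All of this stands, and it is why the correlation is shown as a range.

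It can also be said that the plan does adjust for gestational age. It does, but only beyond about 0.75 SD, so the rule hardly ever acts. Whether it covers secondary outcomes is unclear: the list is tied to the primary outcome, while the rule speaks of main analyses in the plural. The Mann–Whitney fallback takes no covariates, but nothing shows how many outcomes would need it.

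**Conclusion.** The point holds as a weakness of precision and credibility, not of validity. The leading named confounder is left to chance in the design and, in practice, in the analysis too. Under the uniform assumption, roughly one trial in nine would show an imbalance of 5 days or more at term equivalent age, and about 95% of those would be analysed without adjustment. How far this matters for beta power depends on a correlation that the article does not give. At 0.2 it is slight; at 0.4 to 0.6 the lost precision is worth having in a trial with 40 expected completers. The remedy belongs in the analysis model; the randomisation list need not change.

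**What to change.** In the Data analysis section, remove the P < 0.005 trigger for gestational age. State that gestational age at birth (continuous) and gender (the stratification factor) are prespecified covariates in the primary linear model and in the regression models for infant secondary outcomes, whatever the baseline comparison shows. The unadjusted estimate can be reported alongside.

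The cost is two degrees of freedom and a change of wording. Both values are available at baseline, so no extra infants or measurements are needed.

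If enrolment has not begun, adding a two-level gestational-age stratum to the list is optional. It needs a regenerated list and four envelope series, with about 15 infants per stratum, and adds little once gestational age is a covariate. Changing the envelopes during enrolment is not justified by the gain.
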